## Abstract

**Background:**

Pulmonary rehabilitation is widely advocated for people with chronic obstructive pulmonary disease (COPD) to improve exercise capacity, symptoms and quality of life, however only a minority of individuals with COPD are able to participate. Travel and transport are frequently cited as barriers to uptake of centre-based programs. Other models of pulmonary rehabilitation, including home-based programs, have been proposed in order to improve access to this important treatment. Previous studies of home-based pulmonary rehabilitation in COPD have demonstrated improvement in exercise capacity and quality of life, but not all elements of the program were conducted in the home environment. It is uncertain whether a pulmonary rehabilitation program delivered in its entirety at home is cost effective and equally capable of producing benefits in exercise capacity, symptoms and quality of life as a hospital-based program. The aim of this study is to compare the costs and benefits of home-based and hospital-based pulmonary rehabilitation for people with COPD.

**Methods/Design:**

This randomised, controlled, equivalence trial conducted at two centres will recruit 166 individuals with spirometrically confirmed COPD. Participants will be randomly allocated to hospital-based or home-based pulmonary rehabilitation. Hospital programs will follow the traditional outpatient model consisting of twice weekly supervised exercise training and education for eight weeks. Home-based programs will involve one home visit followed by seven weekly telephone calls, using a motivational interviewing approach to enhance exercise participation and facilitate self management. The primary outcome is change in 6-minute walk distance immediately following intervention. Measurements of exercise capacity, physical activity, symptoms and quality of life will be taken at baseline, immediately following the intervention and at 12 months, by a blinded assessor. Completion rates will be compared between programs. Direct healthcare costs and indirect (patient-related) costs will be measured to compare the cost-effectiveness of each program.

**Discussion:**

This trial will identify whether home-based pulmonary rehabilitation can deliver equivalent benefits to centre-based pulmonary rehabilitation in a cost effective manner. The results of this study will contribute new knowledge regarding alternative models of pulmonary rehabilitation and will inform pulmonary rehabilitation guidelines for COPD.

**Trial registration:**

ClinicalTrials.gov:
NCT01423227.

## Background

Chronic obstructive pulmonary disease (COPD) is characterised by exertional dyspnoea, reduced exercise tolerance, marked disability and frequent hospitalisation. The current economic burden of COPD to the health system is considerable, with the majority of costs attributable to hospital use
[1,2]. International guidelines for managing COPD include referral to pulmonary rehabilitation
[3], supported by compelling evidence that such programs deliver improvement in exercise capacity, reduction in breathlessness and improvement in health-related quality of life (HRQOL), irrespective of disease severity
[4]. Pulmonary rehabilitation is also associated with a reduced frequency of acute exacerbations and hospital admissions
[5]. Despite the strong evidence of its benefits, the proportion of people with COPD who receive pulmonary rehabilitation is very small, with estimates from developed countries suggesting that it is delivered to less than 5% of those who would benefit each year
[6,7]. Of those people with COPD who are referred to pulmonary rehabilitation, 8% to 50% will never attend
[8,9], while non-completion rates range from 10% to 32%
[10,11]. The practical reasons for this lack of access include a shortage of programs, particularly in rural and regional centres, and an insufficient number of qualified health professionals. Patient-related barriers to attendance have also been identified, with travel and transport to centre-based programs being the most common obstacles to attendance in this disabled group
[8,10-16].

In view of these barriers, the current model of a centre-based pulmonary rehabilitation program is not addressing the needs of many people with COPD who would benefit from this intervention. If new models are not found, uptake of these programs by patients with COPD will continue to be limited. Home-based, unsupervised pulmonary rehabilitation has been proposed as an alternative model which may enhance access and uptake while containing the rising costs of healthcare associated with COPD
[17-20]. Direct comparison of home and centre-based pulmonary rehabilitation has been explored in four studies
[17-20]. Home-based programs were found to be safe, with improvement in exercise tolerance and HRQOL and reduced symptoms demonstrated in both the home and hospital-based groups. However, only one study was a non-inferiority trial
[18] and important differences between supervised and unsupervised groups may not have been detected in other studies. Of greater importance is that no studies of self-monitored pulmonary rehabilitation have tested an entirely home-based intervention. In previous studies participants in the home training groups were required to attend the hospital for self-management education
[17,18] or weekly monitoring
[19]. These approaches fail to overcome the transport and mobility-related barriers to attendance.

Population ageing and the increasing health care burden associated with chronic disease provide an imperative to allocate our limited resources effectively
[21]. The variety of program models and staffing used for home-based rehabilitation in COPD suggests that costs could vary considerably. One home-based program incorporated frequent home visits from clinicians to supervise exercise
[20], a model which has proved to be more costly than centre-based rehabilitation in patients with cardiac disease
[22]. Self-monitored exercise programs utilising telephone follow up have demonstrated clinical effectiveness
[18], but not all components of pulmonary rehabilitation were delivered at home and no cost comparison to centre-based programs was undertaken. Analysis of the costs of delivery is a critical determinant of whether such a model of care is suitable for implementation in clinical practice.

Comprehensive economic evaluation includes both costs to the healthcare service and the patient
[23]. In addition, cost effectiveness analysis incorporates the evaluation of the impact of an intervention on the patient, to determine if benefits are accrued beyond standard healthcare gains. Such gains may be accessed through measurement of quality-adjusted life years (QALYs) which quantify the benefit gained due to an intervention by measuring the change in quality of life over time. In COPD, centre-based pulmonary rehabilitation (exercise training and education) has been demonstrated to be cost-effective with improvement in QALYs
[24,25]. However, no previous studies have assessed such outcomes for home-based pulmonary rehabilitation.

There is a need for new models of pulmonary rehabilitation which allow all program components to be delivered at home, with proven clinical outcomes and low costs. The aims of this study are to 1) compare completion rates of a home-based self-monitored pulmonary rehabilitation program with a hospital-based, outpatient program in people with COPD; 2) compare the clinical benefits of home-based pulmonary rehabilitation and hospital-based pulmonary rehabilitation and 3) compare the costs of home-based and hospital-based pulmonary rehabilitation. We hypothesise that the proportion of patients who complete pulmonary rehabilitation will be greater in the home-based intervention; the clinical effects on exercise capacity, symptoms and quality of life will be equivalent in both models; and the home-based program will be more cost-effective.

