## Methods

### Design

A randomised, controlled, equivalence trial at two tertiary hospitals (Austin Health and Alfred Health) in Melbourne, Australia.

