### Analysis

Continuous variables will be examined with repeated measures analysis of variance and linear mixed models, as appropriate. The proportion of participants who complete the program will be compared between groups using a chi-squared test and the relative risk of non-completion will be determined. All data will be analysed by intention to treat. A per-protocol analysis will also be conducted to reduce the risk of Type 1 error, as recommended in the CONSORT Extension for reporting of non-inferiority and equivalence trials
[48]. Alpha will be set at 0.05.

Sample size calculations are based on the primary outcome of change in 6MWD. If there is truly no difference in the change in 6MWD between home-based and hospital based groups, then 144 participants are required to be 80% sure that the 95% confidence interval will exclude a difference in means of more than 25 metres. We have recently demonstrated that this is the minimal important difference for 6MWD in our population of patients with COPD
[49]. This assumes a standard deviation of the change in 6MWD of 51 metres
[50]. On the basis of our previous trials in pulmonary rehabilitation
[49,50], we expect 15% attrition from the study; we will therefore randomize a total of 166 participants.

This sample size will also provide appropriate power for the secondary outcomes:

***Completion:*** Data from our centres indicate that only 66% people who are referred to pulmonary rehabilitation take up the referral and complete the centre-based program. Previous studies have documented very high completion rates for home-based programs of over 90%
[18]. Using a more conservative estimate of 85% completion, 144 patients will be required to detect a difference in completion rates between hospital and home-based groups (72 in each group).

***Dyspnoea:*** If there is truly no difference in the change in the dyspnoea domain of the CRQ between home-based and hospital based groups, then 142 participants are required to be 80% sure that the 95% confidence interval will exclude a difference in means of more than 2.5 points. This is the minimal important difference for the dyspnoea domain of the CRQ
[51] and assumes a standard deviation of the change in CRQ dyspnoea of 5.1 points
[50].

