## Discussion

This research will be the first study comparing both the clinical effects and cost effectiveness of delivering pulmonary rehabilitation in the home and hospital settings. With the substantial morbidity and mortality associated with COPD
[2], and the growing proportion of people with COPD, there is an increasing need for cost effective treatment strategies. Pulmonary rehabilitation is a low-cost, vital component of both short and long term management of COPD
[3,29]. Currently, the most common method of delivering pulmonary rehabilitation is a centre-based approach, which may be accomplished within an outpatient hospital department, community centre or private practice
[52]. The lack of access to this intervention for a significant proportion of people with COPD is likely to be a contributing factor to the patterns of decline in exercise capacity and increase in symptoms characteristic of this disease
[3]. In comparing the two modes of delivery on important clinical features and the economic impact to both the patient and the healthcare system, further information on the feasibility of a home-based model of pulmonary rehabilitation will be obtained.

It has been well documented that the effects of pulmonary rehabilitation, including those conducted via a centre-based approach, diminish over time, with deterioration in both exercise capacity and HRQOL within 6 to 12 months of program completion
[53]. One key reason for this decline may be the difficulty in maintaining regular exercise routines and adherence over the longer term
[53]. A critical goal of pulmonary rehabilitation is to both maximize and sustain benefits. It is possible that undertaking pulmonary rehabilitation within the home environment may promote more effective integration of exercise routines into daily life over the longer term. With greater adherence to exercise, the initial benefits of pulmonary rehabilitation may be better maintained.

The results of this study will inform guidelines for the provision of pulmonary rehabilitation in COPD and may have a significant impact on the delivery of healthcare to people with COPD. If it is demonstrated that home-based exercise achieves equivalent clinical outcomes and is cost effective compared to a hospital-based program, this increases the options for the provision of this intervention and may assist in overcoming the most frequently identified barriers to pulmonary rehabilitation.

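### The primary criterion is two-sided equivalence with no non-inferiority reading, and its zero-difference planning value sits uneasily with the expected completion gap under intention to treat

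*Protocol article*

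**What the plan says.** The Design section describes "A randomised, controlled, equivalence trial at two tertiary hospitals". The abstract fixes the endpoint and its timing: "The primary outcome is change in 6-minute walk distance immediately following intervention". The Analysis section gives the one decision criterion, a 95% CI that rules out a mean difference beyond 25 m. It names no direction, so both sides count. The planning value is zero: "If there is truly no difference in the change in 6MWD between home-based and hospital based groups, then 144 participants are required".

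The hypotheses at the end of the Background are mixed. The sentence begins with completion and moves to the clinical effects: "We hypothesise that the proportion of patients who complete pulmonary rehabilitation will be greater in the home-based intervention; the clinical effects on exercise capacity". It then completes the part on clinical effects: "symptoms and quality of life will be equivalent in both models". The Analysis section puts numbers on the completion hypothesis, 66% for the hospital programme and 85% for home. The 66% counts people referred, so it includes failure to take up the referral. All data are analysed by intention to treat, and a per-protocol analysis is also planned.

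The Discussion gives the intended use: "If it is demonstrated that home-based exercise achieves equivalent clinical outcomes and is cost effective compared to a hospital-based program, this increases the options".

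**The concern.** The decision the trial is to inform runs in one direction. Home rehabilitation can be offered as a further option if it does not cost patients an important amount of walking distance. A benefit larger than 25 m would be no reason to withhold it. The stated criterion treats the two sides alike, and the article gives no other reading of the interval.

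This matters because one section plans for a completion advantage at home and also for exactly no difference in 6MWD under intention to treat. If finishing the programme contributes to the 6MWD gain, and gains per completer are similar in the two arms, higher completion moves the expected difference towards home. The stated test then becomes harder to pass while the evidence against an important loss becomes stronger.

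An observed +15 m for home shows the problem. Its 95% CI would run from about -2 to +32 m. That excludes a 25 m loss, yet the only stated criterion is not met. A claim of non-inferiority made at that point would be post hoc.

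**Working it through.** **Inputs.** From the Analysis section: margin 25 m; SD of change 51 m; 80% power; true difference 0; 144 evaluable participants; completion 85% and 66%. The 72 per group is stated for completion and taken to apply to 6MWD. Differences are home minus hospital. The extra gain G of completers over non-completers is not in the document and is assumed.

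**The plan's own figure.** For two one-sided tests at a true difference of 0, n per arm = 2 x [51 x (z(1-a) + z(0.90)) / 25]^2.
- a = 0.05 per side (90% CI): 2 x [2.04 x (1.645 + 1.282)]^2 = 71.3, so 72 per arm and 144 in total. This matches.
- a = 0.025 per side (the 95% CI in the text): 2 x [2.04 x (1.960 + 1.282)]^2 = 87.5, so 88 per arm and 176 in total. This does not match.

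So 144 is a two-sided equivalence size. A non-inferiority size at one-sided 0.025 would be 132. The mismatch between 90% and 95% is a separate matter, but it is why the baseline power below is 67% and not 80%.

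**What passes.** SE = 51 x sqrt(2/72) = 8.5 m. The 95% half-width is 1.96 x 8.5 = 16.66 m. Equivalence needs an estimate within 25 - 16.66 = 8.34 m of zero. With a 90% CI the limit is 25 - 1.645 x 8.5 = 11.0 m.

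**Difference implied by completion.** Gap = 0.85 - 0.66 = 0.19, so d = 0.19 x G. G = 25 m gives 4.75 m and G = 50 m gives 9.5 m. To reach the 25 m margin, G would have to be 25/0.19, about 132 m.

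**Probabilities at 72 per arm.**
- Equivalence = Phi((25-d)/8.5 - 1.96) + Phi((25+d)/8.5 - 1.96) - 1
- Lower limit above -25 m = Phi((25+d)/8.5 - 1.96)
- Upper limit above +25 m = 1 - Phi((25-d)/8.5 - 1.96)

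| True d (m) | Equivalence, 95% CI | Equivalence, 90% CI | Lower 95% limit above -25 m | Upper 95% limit above +25 m |
|---|---|---|---|---|
| 0 | 67% | 81% | 84% | 16% |
| 4.75 | 60% | 74% | 94% | 34% |
| 9.5 | 43% | 56% | 98% | 55% |

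**All 166 analysed (83 per arm).** The SE is 7.9 m and the largest passing estimate is 9.5 m. At d = 0, 4.75 and 9.5 m, equivalence has probability 0.769, 0.689 and 0.491. The lower limit exceeds -25 m with probability 0.885, 0.964 and 0.992. The pattern is the same.

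**A smaller gap.** The Background quotes non-completion of 10% to 32%, separately from never attending. Taken as the hospital rate, that is 68% to 90% completion, and the gap to 85% is +17 to -5 points. For G = 50 m, d is then +8.5 to -2.5 m; for G = 25 m, +4.25 to -1.25 m.

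**The case against.** A reader might infer that the trial's own hypotheses predict a better 6MWD at home. They do not. The hypothesis for clinical effects is equivalence, and a home advantage in 6MWD is only an inference from completion. The Discussion's remark "With greater adherence to exercise, the initial benefits of pulmonary rehabilitation may be better maintained" does not help that reading. It is raised as a possibility for the longer term, whereas the primary outcome is measured straight after the programme.

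The inference is itself open to challenge, for four reasons:
- Participants have consented and finished baseline testing before allocation, so a 66% that includes non-uptake probably overstates the gap among those randomised.
- Completion means at least 70% of planned sessions, so some non-completers will have trained a good deal and G may be small.
- Unsupervised training may yield less per completer, which would offset higher completion and make zero a defensible planning value.
- If the per-protocol set is confined to completers, which the article does not say, that analysis largely removes the mechanism. Its weight in the decision is not stated either.

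All four stand. They reduce the size of the effect and are why it is given as a range.

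It is also fair to say that equivalence was chosen deliberately and used consistently, that losing power as the true difference grows is a property of any equivalence test, and that a published interval would show a home advantage whatever label it carried. So it would be too strong to say that the trial cannot answer its question, or that every home-better result fails: estimates up to about 8.3 m in favour of home pass.

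Finally, a stepwise reading may be set out in an analysis plan that is not shown. If so, nothing needs changing. The point here concerns the criterion and planning value that the article does state, and how they fit the stated use.

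**Conclusion.** The concern holds in a limited form. The one stated criterion is two-sided, has no non-inferiority reading, and serves a decision that runs in one direction. The planned zero difference is not contradicted by the hypotheses, but it sits uneasily with a completion gap of up to 19 points under intention to treat.

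For G = 25 to 50 m, the chance of declaring equivalence with the 95% CI falls from 67% to 60%-43%, while the chance of excluding a 25 m loss rises from 84% to 94%-98%. These figures rest on four assumptions: SD 51 m with 72 evaluable per arm, the full 19-point gap, equal gain per completer in both arms, and G itself. A smaller gap among randomised participants shrinks the effect and could reverse its sign, and the per-protocol analysis would reduce it. The choice of an equivalence design is not an error. What is missing is a pre-stated conclusion for a moderate home advantage.

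**What to change.** Keep the equivalence test, the 25 m margin and the sample size. Before unblinding, state how the same 95% CI for home minus hospital will be read:

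1. Lower limit above -25 m: home is non-inferior.
2. Upper limit also below +25 m: the programmes are equivalent.
3. Lower limit above 0: home is superior.

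With 72 per arm and SD 51 m, estimates within 8.34 m of zero give equivalence. Estimates between 8.34 and 16.66 m in favour of home give non-inferiority only, and larger ones give superiority as well. Read the CRQ dyspnoea domain in the same way with 2.5 points. A higher score is better there too, so the sign carries over.

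The cost is wording only: no further patients or data. The lower limit of the 95% CI keeps the one-sided error for non-inferiority at 2.5%. The downside is that non-inferiority is a weaker conclusion than equivalence and must be reported as such.

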## Methods

### Design

A randomised, controlled, equivalence trial at two tertiary hospitals (Austin Health and Alfred Health) in Melbourne, Australia.

### Participants

To be eligible for enrolment, participants must be greater than 40 years of age, with a diagnosis of COPD based on an FEV_1_/FVC ratio of < 70%
[3] and a smoking history (current or former) of a minimum of 10 packet years. Participants will be excluded if they have 1) diagnosis of asthma, 2) attended a pulmonary rehabilitation program within the last 2 years, 3) experienced an exacerbation of COPD within the last four weeks or 4) have other comorbidities which will prevent participation in an exercise training program.

### Recruitment and randomisation

Potential participants will be identified via attendance at respiratory medicine clinics at the Austin or Alfred Hospitals, upon referral to pulmonary rehabilitation at these sites, or screened from the existing database of the pulmonary rehabilitation programs at each site. Eligible participants will be approached by the researchers who will explain the study and provide participants with written and verbal information. The Human Research Ethics Committees of Alfred Health, Austin Health, La Trobe University and Monash University have approved this study, and written, informed consent will be obtained from all participants. Participants will be randomised to the hospital or the home based group using stratified block randomisation, with stratification for site (Austin or Alfred) and disease severity (FEV_1_ < 50% predicted versus FEV_1_ > 50% predicted)
[3]. Randomisation will be undertaken using a computer generated sequence and allocation will be concealed using sealed, opaque envelopes. Participants will be allocated to groups after completion of baseline assessment. The flow of participants through the study will reflect the recommendations of the Consolidated Standard of Reporting Trials (CONSORT)
[26].

### Interventions

#### Hospital-based pulmonary rehabilitation program

Participants will undertake a twice weekly, 8-week outpatient group-based supervised program, with individually prescribed exercise training and self-management education, to be undertaken at their site of recruitment. The program will follow the guidelines for exercise prescription in COPD
[27]. This will include 30 minutes of aerobic exercise at each session, as well as upper and lower limb strength training, which will be comprised of both functional tasks and free weight training. The initial aerobic exercise prescription for walking will be set at 80% of the speed walked during a 6-minute walk test (6MWT) and at 60% of the maximal work-rate for cycling
[28] and progressed each week according to patient symptoms. Resistance training will utilize functional activities such as stair training and sit to stand from a chair. Participants will be monitored with pulse oximetry during exercise training. Participants will also be encouraged to exercise at a moderate intensity at home an additional three times per week
[27] and this activity will be recorded in a home diary which is reviewed weekly. Skill-orientated education and training sessions conducted by members of the multi-disciplinary team will be provided, with topics consistent with current recommendations
[27,29]. A record of sessions attended by each participant will be maintained. The delivery of the pulmonary rehabilitation is standardised across the two sites following completion of previous collaborative pulmonary rehabilitation trials
[30].

